# Decompressive laparotomy with temporary abdominal closure versus percutaneous puncture with placement of abdominal catheter in patients with abdominal compartment syndrome during acute pancreatitis: background and design of multicenter, randomised, controlled study

**DOI:** 10.1186/1471-2482-10-22

**Published:** 2010-07-12

## Abstract

**Background:**

Development of abdominal compartment syndrome (ACS) in patients with severe acute pancreatitis (SAP) has a strong impact on the course of disease. Number of patients with this complication increases during the years due more aggressive fluid resuscitation, much bigger proportion of patients who is treated conservatively or by minimal invasive approach, and efforts to delay open surgery. There have not been standard recommendations for a surgical or some other interventional treatment of patients who develop ACS during the SAP. The aim of DECOMPRESS study was to compare decompresive laparotomy with temporary abdominal closure and percutaneus puncture with placement of abdominal catheter in these patients.

**Methods:**

One hundred patients with ACS will be randomly allocated to two groups: I) decompresive laparotomy with temporary abdominal closure or II) percutaneus puncture with placement of abdominal catheter. Patients will be recruited from five hospitals in Belgrade during two years period. The primary endpoint is the mortality rate within hospitalization. Secondary endpoints are time interval between intervention and resolving of organ failure and multi organ dysfunction syndrome, incidence of infectious complications and duration of hospital and ICU stay. A total sample size of 100 patients was calculated to demonstrate that decompresive laparotomy with temporary abdominal closure can reduce mortality rate from 60% to 40% with 80% power at 5% alfa.

**Conclusion:**

DECOMPRESS study is designed to reveal a reduction in mortality and major morbidity by using decompresive laparotomy with temporary abdominal closure in comparison with percutaneus puncture with placement of abdominal catheter in patients with ACS during SAP.

**Trial registration:**

ClinicalTrials.gov Identifier: NTC00793715

## Background

There is growing evidence in the literature that development of abdominal compartment syndrome (ACS) in patients with severe acute pancreatitis (SAP) has a strong impact on the course of disease [1-4]. The main causes for development of ACS during the course of SAP are: pancreatic and peripancreatic inflammation, visceral oedema caused by aggressive fluid resuscitation, presence of free fluid collection, and paresis of the bowel. Several studies clearly showed that development of organ failure in SAP is in correlation with presence of intraabdominal hypertension (IAH) [2,3,5,6]. It seems that the number of patients with this complication has increased, due to more aggressive fluid resuscitation, a much bigger proportion of patients treated conservatively or by a minimal invasive approach, and efforts to delay open surgery.

Intra-abdominal hypertension reduces organ perfusion and may cause organ dysfunction [7,8]. Increased intra-abdominal pressure (IAP) leads to hypoperfusion of the gastrointestinal tract and reduction of chest wall compliance [9]. It has also been shown that an IAP above 20 mmHg can lead to oliguria and significant reduction in the cardiac output [10,11]. IAH was associated with significantly higher APACHE II score and MODS score in patients with SAP [3,4]. De Walle et al. [5] published a higher incidence of respiratory, circulatory and renal failure among the patients with IAH. In patients with severe acute pancreatitis, pancreatic perfusion is reduced, and IAH probably contributes to further development of pancreatic hypoperfusion and consequently necrosis.

Some recent studies suggested that ACS is a frequent finding in patients with SAP [3,6,8,12,13]. Tao et al. [8] reported a 36% incidence of ACS among 297 patients with SAP. In a recently published study Al-Barhani et al. [3] showed an incidence of 61% of IAH and 56% of ACS in a selected well-studied and monitored group of SAP patients. However, the lack of a definition of ACS and methodological issues, make interpretation of these results and some other studies difficult.

So far, there have not been standard recommendations for a surgical or some other interventional treatment of patients who develop ACS during the course of SAP [14]. Despite the fact that World Society of Abdominal Compartment Syndrome (WSACS) published definition of IAH and ACS [15] and recommendation for the treatment [16], the appropriate surgical technique for the treatment of those patients suffering from SAP is still debated. Some procedures have been occasionally reported that could be useful and may be able to improve outcome of patients who develop ACS during SAP. Several authors published relief of ACS after insertion of drain under radiological guidance [12,17-19]. Some others recommended decompressive laparotomy with subsequent laparostomy for the treatment of ACS [1,8,20-22]. Several investigators also suggested skin incisions to perform a subcutaneous fasciotomy with the peritoneum left intact [23,24].

Sun et al. [12] performed a randomised study to compare effects of indwelling catheter and conservative measures in the treatment of ACS in fulminant acute pancreatitis. They found that drainage volume was positively correlated with intraabdoninal pressure, which also was correlated with hospitalization time and APACHE II score. Effects of the treatment in the group with abdominal catheter were significantly better than in conservative group, regarding relief of abdominal pain and hospitalization time. In addition mortality rate decreased from 20.7% to 10%, but without significant difference.

Decompressive laparotomy for ACS associated with SAP has not been studied in large patients group [14]. Occasionally, there have been several case reports in the literature with high early mortality rate, ranging from 17 to 75% [1-6,20-22,25]. A high proportion of patients in these reports, during surgical decompression received retroperitoneal debridement and early mortality was mainly associated with uncontrolled retroperiotoneal bleeding [5]. Current very limited experience supports the strategy of decompresive laparotomy in patients with ACS during SAP, but without premature exploration of pancreatic region and retroperitoneum [14].

All these data have not provided enough clear evidence to support a treatment algorithm for ACS in patients with SAP, although two approaches deserve more attention than other. These are decompresive laparotomy with temporary abdominal closure and percutaneous puncture with placement of abdominal catheter. Both of these procedures raise several unresolved issues such as for decompresive laparotomy: a) the relation to potential necrosectomy, b) difficulties in management of semi-open abdomen, c) increased risk of enteric fistulas d) potentially higher number patients with infected pancreatic necrosis than expected e) incidence of postoperative hernias. The main unanswered question for percutaneous puncture with placement of abdominal catheter is whether using this procedure is possible to achieve sufficient decompression and relief of ACS.

We anticipated that decompresive laparotomy with temporary abdominal closure, beside all potentially negative side effects that early open surgery carries in patients with acute pancreatitis, may result in decrease of overall mortality and major morbidity. The DECOMPRESS study is designed to compare effects of decompresive laparotomy with temporary abdominal closure and percutaneous puncture with placement of abdominal catheter in patients with abdominal compartment syndrome during acute pancreatitis.

## Methods

### Study objectives

The objective of this study is to compare outcome of two different interventions in the treatment of abdominal compartment syndrome in patients suffering from acute pancreatitis.

### Primary endpoint

The primary endpoint is mortality rate during the hospital stay for patients with acute pancreatitis.

### Secondary endpoints

Secondary endpoints are duration time of organ failure, development of "new organ failure", number of infectious complications, necrosectomy, enteric fistulas, intensive care stay, and total hospital stay.

### Participants

Patients will be enrolled from five university hospitals from Belgrade, Serbia.

### Inclusion criteria

The study population consists of patients with AP complicated by development of abdominal compartment syndrome. Organ dysfunction (Table 1) in association with intra-abdominal hypertension will define the presence of abdominal compartment syndrome. Intra-abdominal hypertension will be defined as an IAP of 20 mm Hg and higher.

**Table 1 T1:** Definitions of organ failure

Organ Failure	Definition
Circulatory	Systolic blood pressure less than 90 mmHg or need for catecholamine support

Pulmonary	PaO2 60 mmHg or less or need for mechanical ventilation

Renal	Need for hemodialysis or creatinine level greater than 177 umol/L after rehydration

### Exclusion criteria

Patients will not be enrolled to the study if any of the following criteria are present: a) age < 18 and > 80 years; b) recent surgical interventions c) psychoses d) pregnancy e) previously history of chronic pancreatitis.

### Treatment and monitoring before the randomization

All patients with AP will be treated according to pre-established treatment protocol. The treatment protocol for patients with predicted SAP comprising: enteral nutrition preferably via a nasogastric route (in case of intolerance nasojejunal tube will be inserted), an early endoscopic retrograde cholagiopancreatography (ERCP) with sphincterotomy in patients with obstructive cholangitis and/or jaundice and antibiotic prophylaxis. If gastrointestinal nutrition is contraindicated, the patients will receive parenteral nutrition. Patients with predicted mild form of disease will be treated with intravenous fluid and analgetics with close monitoring of vital signs, renal and pulmonary function. Intraabdominal pressure will be monitored routinely on daily basis in all patients with predicted SAP, represented by at least one of the following criteria: APACHE II score ≥ 8, Imrie score ≥ 3 points and CRP ≥ 150 mg/L. In addition, in all patients with clinically suspected intraabdominal hypertension, abdominal pressure will be also measured daily. In all patients who have diagnosed IAH or predicted SAP, SOFA score will be calculated daily. It is well known that, usually abdominal compartment syndrome develops in the very early course of disease (during the first week) and the we expect that vast majority of our patients will be recruited within that time frame. Although, if there will be patients with ACS in later course it will not be an exclusion criteria. Since, many patients will be transferred from referring centres, violation of pre-randomization protocol is not an exclusion criteria.

Intravesical pressure, which indirectly reflects IAP, will be measured using a standard technique that has been described by Cheatham et al. [26] Contrast enhanced CT (CCT) will be done in all patients with IAH, immediately after the diagnosis has been established. This diagnostic toll will be also performed after 7-10 days an all patients with predicted SAP.

Patients with abdominal compartment syndrome will be randomised either for decompressive laparotomy with temporary abdominal closure or percutaneous puncture with placement of abdominal catheter.

### Group A: Decompresive laparotomy with temporary abdominal closure

Laparotomy will be performed via midline incision extending from xyphoid processus until pubis. If ascites is present, it will be evacuated and sent for biochemical and microbiological analysis. Abdominal cavity will be carefully inspected, but any manipulation on necrotic area and lesser sac are not allowed. After cleaning the abdomen, one large bore drain will be placed in the Douglas space. Abdomen will be temporarily closed using an abdominal zipper placed on fascial edges. Abdominal pressure will be measured one hour after surgery and every day at 9 a.m. during next 10 days. Planned staged reoperation will be repeated at 72 h intervals and if it is technically possible abdomen will be definitively closed after 3 reoperation or 9 days, independently of clinical picture and patients conditions. If there is clinical improvement and IAP decreases bellow 15 mm Hg, the abdomen wall will be definitively reconstructed and drain will be taken out, before that period of time. "Clinical improvement" is defined as: no more need for mechanical ventilation, dialysis/hemofiltration and catecholamines for at least 2 days.

### Group B: Percutaneous puncture with placement of abdominal catheter

Insertion of abdominal catheter diameter will be performed percutaneously 2 cm bellow the umbilicus. Fluid collected during drainage will be sent for biochemical and microbiological analysis. The abdominal catheter will be removed after 9 days. Measurement of intraabdominal pressure will be done in the same time interval as in group A.

### Management after the intervention

Post interventional management will be similar in both groups. All necessary intensive care measures will be continued and SOFA score will be calculated daily. In patients with further clinical deterioration or with clinical signs of infection/sepsis careful microbiological and CCT examination will be performed. After exclusion of other infection causes such as urinary tract, lungs and intravenous catheters, ultrasound guided fine-needle aspiration (FNA) of the pancreatic necrosis with consecutive Gram stain and bacteriologic culture will be carried out. If the infection of pancreatic necrosis is suspected, either by positive microbiological FNA findings or presence of gas in necrotic area on CCT, surgical intervention will be indicated. If the presence of infected necrosis is suspected during first 2 weeks of treatment, surgery may be postponed until third week of treatment. Standard surgical procedure will be maximal necrosectomy followed by continuous closed lavage. During surgery, at least two smears for bacteriologic culture will be taken from the area of pancreatic/peripancreatic necrosis.

### Data collection and follow-up

This study is coordinated by Emergency Surgical Department, Clinical Center of Serbia and School of Medicine, University of Belgrade. The clinical data of all randomized patients will be collected centrally in a database at the Emergency Surgical Department, Clinical Center of Serbia and School of Medicine, University of Belgrade. Trial coordinator will be in regular contact with the participating centers and will monitor the data of the every randomized patient.

Patients will be monitored during their hospital stay. For both, primary and secondary endpoints, follow-up will be finished at hospital discharge or death. Routine follow up visit are planned 3 and 6 month after discharge, including physical examination, abdominal ultrasound and/or CCT and/or MRI examination, to exclude presence of incisional hernias and pancreatic pseudocyst or other post-pancreatitis complications.

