### Sample size calculation

The sample size calculation is based on equivalence design for the primary endpoint- mortality rate of patients with abdominal compartment syndrome during acute pancreatitis. It is anticipated that decompressive laparotomy with temporary abdominal closure will lead to a mortality rate reduction from 60% of patients to 40%. Therefore, the expected reduction in mortality that was used for sample size calculation is 20%. With calculated 80% power of the study (beta error 0.20) and alpha error of 0.05 (two-sided) complete data from 47 patients per group will be necessary to demonstrate this effect, if it truly exists. Taking into account a 7% loss-to-follow up, a total of 2 × 50 patients have to be randomized.

Reported annual rate of treated patients with severe form of acute pancreatitis is about 250 (based on hospital data of Emergency Centre, Clinical Centre of Serbia, 3 affiliated hospitals of School of Medicine University of Belgrade and Military Academy), while the prevalence of abdominal compartment syndrome in this patient population is about 20%. Consequently, the total expected number of patients with abdominal compartment syndrome during acute pancreatitis in these 5 centres is about 50, annually. Based on this assumption, the expected study inclusion period would be ended in two years.

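### Endpoint follow-up ends at discharge, so the mortality window varies with length of stay and laparotomy's late harms fall outside every endpoint, although 3- and 6-month visits are planned

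*Protocol article*

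**What the plan says.** The Primary endpoint section reads: "The primary endpoint is mortality rate during the hospital stay for patients with acute pancreatitis". No number of days is given. Data collection and follow-up sets the cut-off: "For both, primary and secondary endpoints, follow-up will be finished at hospital discharge or death". The next sentence continues past that point: "Routine follow up visit are planned 3 and 6 month after discharge", with examinations and imaging "to exclude presence of incisional hernias and pancreatic pseudocyst or other post-pancreatitis complications".

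The Background lists unresolved issues for laparotomy, among them enteric fistula and "e) incidence of postoperative hernias". The Secondary endpoints section names duration of organ failure, new organ failure and "number of infectious complications, necrosectomy, enteric fistulas, intensive care stay, and total hospital stay". Fistula and necrosectomy are on that list; hernia is not.

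Statistical analysis compares in-hospital mortality by relative risk and a two-sided test, adds Kaplan-Meier curves with a log-rank test, and compares intensive care and total hospital stay between arms. It mentions no analysis of the 3- and 6-month findings.

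**The concern.** Two things follow from the cut-off.

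First, the time at risk of a primary event is the length of stay. That is a post-randomisation quantity which the trial itself treats as an outcome. The two pathways differ early on: planned reoperations and abdominal closure in one arm, a catheter in the other. Discharge timing may therefore differ by arm. If it does, in-hospital mortality mixes the risk of dying with the speed of discharge. The survival analysis has a related problem. Patients leave hospital because they have recovered, so censoring them at that moment lets the sicker patients still in hospital stand in for them.

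Second, the article presents the trial as a test of whether laparotomy lowers mortality and major morbidity. Incisional hernia is a harm that belongs mainly to the laparotomy arm, and it is looked for after discharge. A comparison that closes at discharge leaves it out, together with any fistula, necrosectomy or readmission that comes later.

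**Working it through.** The document gives no length of stay and no death rate after discharge, so it has no figure of its own to reproduce on this point. Steps 2 to 4 use assumed rates, marked as such, and show what the design can and cannot tell apart.

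**1. Patients whose later course is outside every endpoint.** Inputs from Sample size calculation: mortality 40% (laparotomy) and 60% (catheter), 50 randomised per arm.
- Laparotomy: 50 × (1 − 0.40) = 30 discharged alive.
- Catheter: 50 × (1 − 0.60) = 20 discharged alive.

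**2. Discharge timing and in-hospital mortality.** Assume constant daily hazards in hospital, h for death and d for discharge. Then in-hospital mortality = h / (h + d). Take h = 0.02 in both arms.
- d = 0.02: 0.02 / 0.04 = 50%.
- d = 0.03: 0.02 / 0.05 = 40%.
- d = 0.04: 0.02 / 0.06 = 33%.

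With the same daily risk of death in hospital, discharge at 0.02 versus 0.03 gives a 10-point gap, and 0.02 versus 0.04 a 17-point gap. The trial's target effect is 20 points.

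**3. What that gap means depends on the unobserved period.** Take the 0.02 versus 0.03 case and ask for mortality by day 90.
- If the same hazard continued after discharge: 1 − exp(−0.02 × 90) = 83% in both arms. The in-hospital gap would be pure artefact.
- If nobody died after discharge: 0.50 × (1 − exp(−0.04 × 90)) = 49% versus 0.40 × (1 − exp(−0.05 × 90)) = 40%. The gap would be real.

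These are extremes, and the first is unlikely if discharge follows recovery. Data that end at discharge cannot tell them apart; vital status at a fixed time can.

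**4. Kaplan-Meier and log-rank.** With discharged patients censored, the hazard estimated in step 2 is 0.02 in both arms. The curve would show 83% dead by day 90 in each arm, and the log-rank test would have no difference to detect. If discharged patients in fact survive, the true day-90 figures are the 49% and 40% of step 3. So censoring at discharge can overstate mortality, and can disagree with the primary comparison in the same patients.

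**5. Cost of going further and replacing the primary endpoint.** The usual two-sided formula is n per arm = [1.96 √(2p̄(1 − p̄)) + 0.84 √(p₁(1 − p₁) + p₂(1 − p₂))]² / (p₁ − p₂)². For 60% versus 40% at 80% power it gives 97, where the article states 47. That discrepancy is a separate matter, and this point does not rest on it. With assumed death rates after discharge of qA (laparotomy) and qB (catheter), fixed-horizon mortality is 0.40 + 0.60 qA and 0.60 + 0.40 qB:

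| qA / qB | Mortality | n per arm | Power at 47 per arm |
|---|---|---|---|
| 0 / 0 | 40% vs 60% | 97 | 0.49 |
| 5% / 5% | 43% vs 62% | 108 | 0.45 |
| 10% / 10% | 46% vs 64% | 119 | 0.42 |
| 10% / 0 | 46% vs 60% | 199 | 0.27 |

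**6. Loss allowance.** 50 × (1 − 0.07) = 46.5, already just under the 47 required, so there is no slack for further loss after discharge.

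**7. Feasibility of day 90.** Discharge comes after randomisation, so a visit 3 months after discharge falls at about day 90 from randomisation or later. Patients still in hospital at day 90 have known status.

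**The case against.** In-hospital mortality is a recognised endpoint, and the article uses it consistently in its abstract, endpoint, follow-up and analysis sections. Closing endpoints at discharge and then holding routine visits is not a contradiction. This stands, and it is why the primary endpoint should stay. Replacing it would also reopen the 60% and 40% assumptions, as step 5 shows.

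Most deaths may be early. The article expects the syndrome mainly in the first week and cites high early mortality after decompression. This is plausible and would limit the effect on mortality, but the document gives no figure to settle it. The hazards in steps 2 to 4 are illustrations, not estimates.

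The late findings are collected, and a full protocol or analysis plan that is not shown could tabulate them. That is fair. However, the stated cut-off covers all primary and secondary endpoints, so such a table could not make them endpoints without changing the rule.

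Four stronger readings are tempting but not supported:
- **Back-transfer deaths counted as survivors.** The article says that "many patients will be transferred from referring centres", but this describes transfer into the trial hospitals before randomisation. Transfer back is not mentioned.
- **Mortality biased towards laparotomy.** The direction is unknown. If reoperations lengthen the stay, that arm is observed longer and more of its deaths are counted.
- **Late harms wholly ignored.** Fistula and necrosectomy before discharge are endpoints; only later events, and hernia, are left out.
- **The existing allowance pays for the extension.** The words "Taking into account a 7% loss-to-follow up" sit oddly beside an endpoint that ends at discharge, but nothing shows that 7% would cover loss to 90 days or 6 months.

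**Conclusion.** The concern holds in a limited form. The stated cut-off gives the primary endpoint an observation window that varies with length of stay, makes censoring at discharge informative for the survival analysis, and leaves hernia and post-discharge fistula or necrosectomy outside every endpoint. The harm comparison is therefore incomplete on the laparotomy side.

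For mortality, neither direction nor size can be derived from the document. The 10- and 17-point gaps rest on assumed constant hazards and on different discharge rates between arms. The count of about 30 and 20 survivors rests on the article's own planning rates. The point does not invalidate in-hospital mortality as the primary endpoint. It identifies an inexpensive improvement that uses visits already planned.

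**What to change.** Keep in-hospital mortality as the primary endpoint and amend three sections:
- **Secondary endpoints:** add all-cause death by day 90 from randomisation. Add incisional hernia and readmission, and count enteric fistula and necrosectomy up to the 6-month visit.
- **Data collection and follow-up:** limit the discharge cut-off to the primary endpoint and the in-hospital measures. Extend follow-up for the other secondary endpoints to the 6-month visit, and record vital status at day 90 for every randomised patient, including those who miss visits.
- **Statistical analysis:** run Kaplan-Meier and log-rank to day 90 from randomisation without censoring at discharge, and compare the late harms by arm.

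The cost is protocol wording, a vital-status query and some missing data after discharge, which the 7% allowance may not cover. No new visits are needed, and the sample size basis for the primary endpoint is untouched by this change.
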